## Abstract

**Trial registration:**

Clinical Trial Registry-India (CTRI) CTRI/2024/03/063824

## Introduction

Women’s reproductive health is a significant issue in India. Women of reproductive age constitute 22.2% of the total population. To ensure the population’s growth and development, the country has a lot of work to perform. Many studies on women’s health coverage programs in India have been done to understand the problems. Over the past 20 years, India has experienced increased economic growth, but it has performed poorly in terms of health and human development indexes. Access to healthcare and significant health inequities have become worse and persisted across states’ communities. In tribal areas, there are disparities in maternal health care utilization, lack of accessibility to safe menstrual health, malnutrition, and low in contraceptive usage.

The maternal mortality ratio of Jharkhand state showed a declining trend (56 per lakh live births) compared to India (97 per lakh live births) as per Sample Registration System (SRS): 2018–20 [1]. However, the use of “*Maternal Child Health services”* in Jharkhand is lagging. National Family Health Survey (NFHS)-5 data showed the percentage of mothers who had at least four Antenatal Care (ANC) visits is 54.2 in India, whereas it is only 36.4% in Jharkhand. Similarly, rural Jharkhand has 92.3% of registered pregnancies, but only 36.4% had four ANC visits, 13.2% of mothers consuming “Iron Folic Acid” for 180 days (about six months), at the time they were pregnant, and 66.7% *of* mothers received postnatal care^2^. In terms of lack of accessibility to safe menstrual health, a study context to the rural part of West Singhbhum found that 38% of the adolescent girls were anemic, and 27% of the adolescent girls use local napkins during their menstruation [2]. Anemia in pregnant women (15–49 years old) is 59.2% and in adolescent girls (15–19 years) is 66.7% respectively according to the Jharkhand NFHS 5 report, this is slightly higher from the Indian context with 54.3% and 60.2% respectively [3]. Whereas it was found that rural women with Body Mass Index below normal was 29.2% as compared to the overall India context with 21.2%. The percentage of male sterilization is 0.2% in rural areas of Jharkhand followed by female sterilization at 0.4%, condom usage at 3.5%, and pill usage at 3.1% only. Healthcare providers discussed family planning with non-user females. in rural areas of Jharkhand is 29.5% reported from NFHS 5 report [3].

On literature search various evidence were reported regarding the reproductive healthcare service disparities among the tribal communities of India. As per one of the survey carried out in India discovered the considerable caste/tribe disparities among the use of “Maternal Child Health care services” in the chosen Indian states. The main causes for the under-utilization of “these services”, particularly, for members of marginalized social groups, having restricted availability & the absence of comprehensive healthcare [4]. Another study analyzed the level of disparity in maternal health care, including complete antenatal care (full ANC), Skilled Birth Attendants (SBA), and Postnatal Care (PNC) in rural India [5]. A qualitative study was done in Uttar Pradesh regarding “Accessibility of Reproductive Health Related Schemes for Pregnant and Lactating Rural Women”, it was found that the study focused into the way women experienced access and hurdles in using health care schemes [6]. Another study was conducted in the three Indian states of “*Madhya Pradesh”, “Jharkhand”, and “Chhattisgarh”*, which are inhabited by tribes. The main aim of the current study was to analyze the variables influencing the use of maternal health services. The “National Family Health Survey” data were taken in the study. According to the study findings, there were larger “socio-economic” disparities in the use of MCH services in each of the three states that were the subject of the investigation. As per the “regression” analysis, people living in the tribal area are less likely than other caste groups to use maternal and child health care facilities and benefits [7]. Therefore, a study stated that one of India’s most fragile and impoverished states is Jharkhand. There aren’t many community-based programs and campaigns that prioritize adolescent and youth public health issues like gender and sexuality [8].

However, there are some major health coverage schemes running in India to improve the health of a reproductive age group women, such as Janani Suraksha Yojana, Janani Sishu Swasthya Karyakram, Pradhan Mantri Matri Vandana Yojana, Rashtriya Kishori Swasthya Karyakram, Poshan Abhiyan, Anemia Mukt Bharat.

Hence this research will aim to study the utilization of healthcare schemes among tribal reproductive-age groups in Jharkhand. Based on the findings a health awareness booklet will be developed and validated. Our study can contribute to designing effective interventions and policies that cater to the specific needs of tribal communities, ultimately improving their access to quality healthcare services. Research on the knowledge, attitude, and practices towards health coverage schemes in tribal regions of India is essential for addressing health disparities. Improving awareness and understanding, overcoming attitudinal barriers, informing policy development, and promoting equity and social justice in healthcare are some of the disparities. It can contribute to designing effective interventions and policies that cater to the specific needs of tribal communities, ultimately improving their access to quality healthcare services.

This research will aim to study the utilization of healthcare schemes among tribal reproductive-age groups in Jharkhand. Based on the findings a health awareness booklet will be developed and validated. Our study can contribute in designing effective interventions and policies that cater to the specific needs of tribal communities, ultimately improving their access to quality healthcare services. Therefore, this study will help to increase in knowledge, awareness, and attitude for reproductive age group tribal women health coverage schemes in the regional language with more pictorial content that can be understood easily.

### Objectives

#### Phase 1: Need assessment.

1. To assess the knowledge, attitude, and practices of healthcare schemes among tribal women in the reproductive age group.2. To understand facilitators and challenges in provision of tribal reproductive age group women healthcare schemes from different stakeholder perspectives.

#### Phase 2: Development & Validation.

3. To develop & validate the awareness booklet for the tribal women of reproductive age group and evaluate the perception of participants towards it.

## Methods/design

We will follow the research design as “Sequential Explanatory Design” [9]. Leading to the generation of evidence for the development of a validated health awareness booklet for tribal women. This study protocol is a part of a Ph.D. project, and the study protocol was prepared and approved from the Institutional Scientific Committee (ISC) on 16^th^ August 2023, followed by the approval from Institute Ethics Committee (IEC) with IEC Number MTMC/IEC/2023/53and the University.

The starting of the recruitment period for this study is as follows: the data collection under phase 1, Objective 1(Quantitative part) was started from 2^nd^ March 2024 and ended on 2^nd^ September 2024. Further, followed by Objective 2 (Qualitative aspect) and under phase 2, Objective 3: Development and Validation of the health awareness booklet for tribal women is planned to complete by 30^th^ October 2026. The timeline for the research protocol will be three years as illustrated in (Fig 1).

**Fig 1 pone.0322777.g001:**
[figure not shown]
Timeline of the completion of work based on SPIRIT guidelines.

### Study setting

The study will be conducted among tribal women in the reproductive age group (15–49 years) and tribal adolescent girls (10–19 years) residing in the field practice area of the Department of Community Medicine. The population comprises individuals from various tribal communities, including Santhal, Ho, Munda, Bhumij, Kharia, and Sabar tribes. The predominant languages spoken in the region are Santhali, Ho, Mundari, Bangla, and Hindi, reflecting the rich linguistic diversity of the area. The primary livelihood of the population includes agriculture, daily wage labor, and homemaking, which are influenced by the socio-economic and cultural fabric of the tribal communities. Geographically, the region is characterized by a mix of plateau, plain, and forested terrain, shaping the lifestyle and accessibility to health services.

### Sampling

East Singhbhum is a district located in the state of Jharkhand. It consists of two sub-divisions, Dalbhum and Ghatsila. Comprising of 11 blocks, Potka, Golmuri cum Jugsalai, Patamda, Ghatsila, Boram, Musabani, Dumaria, Bharagora, Dalbhumgarh, Chakulia, and Gurbandha. A total of twelve villages will be taken from the two randomly selected blocks. The sampling frame for objective one will consists of the list of adolescent girls and reproductive age group women. For the qualitative aspect objective two, the sampling frame will include other stakeholders such as the Block Program Manager/Officer, Block Trainer, Accredited Social Health Activist (ASHA), Auxiliary Nurse Midwifery (ANM), Aanganwadi Workers (AWW), Medical Officer, Village head, and the Tribal women of reproductive age group. Statistical analysis for objective 1 and 3 (feedback form), will be descriptive data analysis and chi-square test to know the association between two variables. Whereas, for objective 2, qualitative data thematic analysis will be done based on codes generated from the transcripts. In objective 1 the study design will be cross-sectional study. Population covered will be the adolescent girls (10–19 years) and reproductive age group (15–49 years) tribal women belonging to following tribes: Santhal, Ho, Munda, Bhumiz, Kharia, and Sabar. Following religion such as Sarna Dharam, Christianity, or Hinduism. Study Participants who will give consent to participate in the study. Migrant population and tribal women suffering from any mental illness will be excluded from the study.

The sample size was calculated through an online tool calculator.net keeping the level of confidence (z) at 95%, and marginal error(E)at 5%, population proportion 50% and population size 258454 [10]. Considering the drop out of 20%, with design effect of 1.5, the sample size becomes 385 (385 + 337) = 722 rounding up to 745. Formula used: n= (Z_1-α/2_)^2 *^ p(1-p)/d^2^. Where n = sample size, Z = level of confidence, E = marginal error, P = Population proportion [11].

Simple random sampling and stratified sampling technique will be used. Out of two blocks, twelve villages will be chosen at random, six village from each block. From each village there will be stratified into two strata, tribal adolescent girls (n = 32/village) and tribal women of reproductive age group. (n = 30 per village). Sampling technique is depicted in form of flow chart mentioned in (Fig 2).

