**Fig 2 pone.0322777.g002:**
[figure not shown]
Simple random sampling and stratified sampling technique.

A Self-administered questionnaire will be used, and in case of illiterate study participants, questionnaire form will be filled by the interviewer/ or the person who will be going to collect the data, on behalf of study participant. Validation of the developed questionnaire will be through the external subject experts and finding the Content Validity Index (CVI) score. Reliability check of the questionnaire will be done through piloting among 10 percent of the study participants from the sample size of the main study and Cronbach’s alpha score will be derived. Domains of the questionnaire will **c**omprise of two sections, Section A- socio-demographic details and section B- Baseline survey consisting of questions on knowledge, attitude, and practices of tribal women towards relevant eight reproductive healthcare schemes of India.

Details of the eight reproductive healthcare schemes included are mentioned in Table 1. Participatory Information Sheet (PIS) will be explained, and Informed Consent (IC) will be taken from the study participants. Data will be collected based on the questionnaire. A total of 20–30 minutes will be given to the study participants and a maximum of 10–15 days per village will be given to collect the data. Quantitative data analysis in terms of frequency, percentage, proportion and for categorical data chi square test will be done. KAP score will be calculated and based on the median and interquartile range which will be finally interpret as low, moderate and high KAP score. All quantitative analysis will be through Jamovi software (Version solid 2.2.5).

**Table 1 pone.0322777.t001:** Healthcare schemes for reproductive age group tribal women in India.

Schemes for Adolescent Girls (10–19 Years)	Schemes for reproductive age group women (15–49 Years)
1.Rashtriya Kishori Swasthya Karyakram	1.Janani Suraksha Yojana
2.POSHAN Abhiyan	2.Janani Sishu Suraksha Karyakaram
3.Anemia Mukt Bharat	3.Pradhan Mantri Matru Vandana Yojana
	4.Pradhan Mantri Surakshit Matritva Abhiyan
	5.Family Planning Schemes under NHM including: a. ASHA Scheme b. Enhanced Compensatory Scheme
	Anemia Mukt Bharat

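### The sample size allows for clustering in 12 villages, but the stated chi-square test ignores it and is too liberal for factors that differ mainly between villages

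*Protocol article*

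**What the plan says.** The Sampling section of the protocol article describes a multistage sample. Two of the district's 11 blocks are drawn at random, and then "twelve villages will be chosen at random, six village from each block". Each village contributes two strata: "tribal adolescent girls (n = 32/village" and 30 women of reproductive age, so 62 people per village.

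The sample size starts from a single-proportion formula, "keeping the level of confidence (z) at 95%, and marginal error(E)at 5%, population proportion 50% and population size 258454", and is then enlarged: "Considering the drop out of 20%, with design effect of 1.5", giving "the sample size becomes 385 (385 + 337) = 722 rounding up to 745".

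The same section fixes the analysis for Objective 1 and for the Objective 3 feedback form as "descriptive data analysis and chi-square test to know the association between two variables". The text after Figure 2 repeats this: "Quantitative data analysis in terms of frequency, percentage, proportion and for categorical data chi square test will be done". It adds that Jamovi will be used for all quantitative analysis. Neither place names an adjustment for village or block.

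**The concern.** The plan accepts, when it sets the sample size, that people in the same village resemble each other enough to inflate variances by half. It then names a test whose null distribution assumes independent people. The two statements do not fit together.

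At stake are the associations with knowledge, attitude and practice (KAP). If a factor differs mainly from village to village, the ordinary chi-square counts each person as separate evidence, although the real comparison is between a dozen villages. Such factors would be declared associated with KAP too often. The Discussion offers the findings to policymakers, and Phase 2 builds the booklet on the survey results, so a false association could carry forward.

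**Working it through.** **1. Is the design effect really in the sample size?** Inputs from the Sampling section: z = 1.96, p = 0.5, d = 0.05, design effect 1.5, dropout 20%.

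- n0 = 1.96² × 0.25 / 0.05² = 384.1, rounded up to 385.
- 385 × 1.5 = 577.5.
- 577.5 / (1 − 0.20) = 721.9, so 722.

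This reproduces the stated 722, so the allowance for clustering is in the number. (The final 745 is close to 12 × 62 = 744.)

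**2. Size of the ordinary chi-square for a factor constant within villages.** With a design effect D, the Pearson statistic behaves approximately as D times a chi-square variable, so the true size is P(χ² > c/D), where c is the nominal 5% critical value. At D = 1.5:

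| df | c | c / 1.5 | true size |
|---|---|---|---|
| 1 | 3.841 | 2.561 | 11.0% |
| 2 | 5.991 | 3.994 | 13.6% |
| 4 | 9.488 | 6.325 | 17.6% |

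**3. Implied ICC.** The protocol gives none. From D = 1 + (m − 1) × ICC with m = 62, ICC = 0.5 / 61 = 0.008. If 1.5 is taken to apply to one stratum of 30 to 32 per village, ICC is 0.016 to 0.017. With assumed ICCs of 0.01, 0.02 and 0.05 at m = 62, D is 1.61, 2.22 and 4.05, and the 1-df size is 12%, 19% and 33%.

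**4. Other kinds of factor.** A simulation of the ordinary chi-square (12 villages × 62 people, outcome prevalence 50%, 4,000 replicates) gave these rejection rates under no association:

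| Factor | outcome ICC 0.008 | outcome ICC 0.05 (assumed) |
|---|---|---|
| Block | 10.9% | 34.0% |
| Partly clustered by village (factor ICC 0.2, assumed) | 6.4% | 12.0% |
| Balanced within villages | 5.4% | 4.8% |

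**5. Intervals, if any are reported.** At D = 1.5 a nominal 95% simple-random-sample interval covers 2Φ(1.96/√1.5) − 1 = 89.0%. At p = 0.5 and n = 745:

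- ignoring clustering: half-width 1.96 × √(0.25/745) = 3.6 points;
- with D = 1.5: 1.96 × √(0.25 × 1.5/745) = 4.4 points;
- with D = 1.5 and t on 10 df (2.23): 5.0 points.

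The effective sample size is 745 / 1.5 = 497.

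**6. Objective 3.** The article takes 12 to 13 people per village for the booklet pilot. With m = 12.5 and ICC 0.008, D = 1 + 11.5 × 0.0082 = 1.09, and the 1-df size for a village-level factor is about 6%. Training is given at one session per village, which could raise the ICC. At an assumed 0.02 to 0.10, D is 1.23 to 2.15 and the size 8% to 18%.

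**The case against.** **The article is condensed and a fuller analysis plan may adjust for clustering.** This would answer the point if the article left the method open. It does not: it names the test twice and the software once. A plan that adjusted for clustering would have to change the stated method.

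**The survey is descriptive.** No primary hypothesis or decision threshold hangs on a chi-square p-value, and ignoring clustering in the variance leaves the point percentages unchanged. This stands and limits the severity.

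**The headline error rates are a worst case.** This also stands. They need a factor constant within villages and all 62 people per village pooled. The protocol does not say which variables will be tested. If girls and women were analysed separately (an assumption, though Table 1 gives them largely different schemes), about 31 per village at ICC 0.0082 gives D = 1 + 30 × 0.0082 = 1.25 and a 1-df size of 7.9%.

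A reader might infer more than the document supports:

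- That tribe, religion or access to services follow village lines. The article lists tribes and religions and mentions varied terrain, but does not say how they are distributed across villages.
- That each village has a single ASHA, ANM and Anganwadi worker, and hence strong clustering. The one-per-village figures are interview quotas for Objective 2, not staffing.
- That planned confidence intervals are too narrow. None is explicitly planned. The 95% level and 5-point margin are sizing inputs.

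**Conclusion.** The point holds, with limits. The stated analysis ignores clustering that the plan's own sample size assumes. For factors that differ mainly between villages (block certainly; tribe, religion or access only if they cluster), the nominal 5% test has a true size of up to 11.0%, 13.6% or 17.6% at 1, 2 or 4 df. These figures rest on the plan's own design effect of 1.5; a larger ICC would make them worse. For partly clustered factors the inflation is small at the implied ICC, and for factors balanced within villages it is negligible. It would therefore be wrong to conclude that every chi-square in the study is invalid.

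The 89% coverage figure applies only if simple-random-sample intervals are put on the percentages.

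Severity: should be fixed. The stated method is mismatched to the design, but the survey is mainly descriptive and the remedy lies wholly in the analysis.

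**What to change.** - Replace the ordinary chi-square for Objective 1 with a cluster-adjusted test: a Rao–Scott chi-square with village as the clustering unit, or a mixed model with a village random intercept.
- Compute any interval for a KAP percentage with village-clustered standard errors and a t reference.
- Report the observed design effects beside the assumed 1.5.
- Do the same for the Objective 3 feedback data.
- State the reach of the inference. Treating block as a fixed stratum leaves 12 − 2 = 10 df (t = 2.23) and limits conclusions to the two selected blocks. Because the blocks were themselves drawn at random, inference to the whole district would rest on two first-stage units, or 2 − 1 = 1 df, which is too few to be reliable.

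Cost: no new data, since village is known from the sampling. The analysis needs a survey or mixed-model routine instead of the default chi-square. Intervals widen (from 3.6 to about 5.0 points at n = 745, D = 1.5 and 10 df), and some associations will lose significance.

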**Fig 2 pone.0322777.g002:**
[figure not shown]
Simple random sampling and stratified sampling technique.

A Self-administered questionnaire will be used, and in case of illiterate study participants, questionnaire form will be filled by the interviewer/ or the person who will be going to collect the data, on behalf of study participant. Validation of the developed questionnaire will be through the external subject experts and finding the Content Validity Index (CVI) score. Reliability check of the questionnaire will be done through piloting among 10 percent of the study participants from the sample size of the main study and Cronbach’s alpha score will be derived. Domains of the questionnaire will **c**omprise of two sections, Section A- socio-demographic details and section B- Baseline survey consisting of questions on knowledge, attitude, and practices of tribal women towards relevant eight reproductive healthcare schemes of India.

Details of the eight reproductive healthcare schemes included are mentioned in Table 1. Participatory Information Sheet (PIS) will be explained, and Informed Consent (IC) will be taken from the study participants. Data will be collected based on the questionnaire. A total of 20–30 minutes will be given to the study participants and a maximum of 10–15 days per village will be given to collect the data. Quantitative data analysis in terms of frequency, percentage, proportion and for categorical data chi square test will be done. KAP score will be calculated and based on the median and interquartile range which will be finally interpret as low, moderate and high KAP score. All quantitative analysis will be through Jamovi software (Version solid 2.2.5).

**Table 1 pone.0322777.t001:** Healthcare schemes for reproductive age group tribal women in India.

Schemes for Adolescent Girls (10–19 Years)	Schemes for reproductive age group women (15–49 Years)
1.Rashtriya Kishori Swasthya Karyakram	1.Janani Suraksha Yojana
2.POSHAN Abhiyan	2.Janani Sishu Suraksha Karyakaram
3.Anemia Mukt Bharat	3.Pradhan Mantri Matru Vandana Yojana
	4.Pradhan Mantri Surakshit Matritva Abhiyan
	5.Family Planning Schemes under NHM including: a. ASHA Scheme b. Enhanced Compensatory Scheme
	Anemia Mukt Bharat

For Objective two the research design included a Phenomenological approach, through this study participant can express there experienced field perspectives related to facilitators and challenges faced. The study population will cover tribal women of reproductive age group (1/village) and adolescent girl(1/village), Block program manager/officer (1/block), block trainer (1/block), Accredited Social Health Activist (1/village), Auxiliary Nurse Midwifery (1/village), Aanganwadi Workers (1 per village), Medical Officer (1/block), and Village Leader (1/village). Purposive sampling will be done. 5–8 interviews per village will be done till the saturation of data over one year to collect and analyze it further. Interviewer’s guide comprising of open-ended questions will be used for an in-depth interview with the broad domains including Demographic details. In-depth interview guide will be based on the Strength, Weakness, Opportunities, and Challenges (SWOC) faced in provision of tribal women.

The researcher will go to the assigned community settings after seeking permission from the State tribal Welfare Commissioner, District Surgeon, Deputy Commissioner, and from Medical Officer In-charge (MOIC). Qualitative data will be collected by In-depth interviews of the study population after explaining the Participatory Information Sheet (PIS) and undertaking the signatures in the Consent forms. Approximately, 20–30 minutes will be given for the interview. Thematic analysis will be done through Atlas ti Software (Version 8).

Phase 2 will be the Development and Validation phase. Based on the results of survey among tribal women and in-depth interview of all the stake holders, a health awareness booklet will be developed on various schemes targeted for adolescent & reproductive age group tribal women mentioned in Table 1. The booklet will contain the information such as benefits and procedures to avail the incentives along with the strategies to overcome the challenges in utilization of services in the eight health schemes selected for the study. Booklet will be validated by the subject experts and piloted among the study participants. Booklet will also discuss about the clinical features covering sign symptoms, diagnosis, and treatment modalities available for any health-related events, the benefits along with the consequences of non-utilization of services benefits of the schemes will also cover the impact of the related events, the benefits along with the consequences of non-utilization of services in terms of adverse health outcomes.

Validation of the booklet will be done with the help of a group of experts (6–10) and by piloting among the study participants. Content validity tools will be used to validate the booklet with the Item generation (through existing literature, previous research, expert knowledge), expert panel review with the help of subject experts, health professional, medical education experts and researcher will review the item, and the rate/rank will be allotted based on their judgement, item selection and modification by refining and revision based on expert comments, and Content Validity Index (CVI) Calculation will be done. Piloting of the booklet developed will be done in the study population (reproductive age tribal women and adolescent girls). Around 20% of the study participants will be included from the main sample size 745. Total 149 rounding up to 150, 12–13 participants per village from 12 villages will be taken. Hence the sampling method used here will be stratified sampling technique and simple random sampling. A series of training sessions (one per each village each of two hours session) will be conducted for the adolescent girls and reproductive age women. Training sessions will be through interactive sessions, Nukkad Natak (street play) along with Audio/Visual clips of the booklet in the local language. The sessions will include briefing on the content, utilization, challenges and ways to address the healthcare schemes mentioned in the booklet. Training and awareness sessions will be delivered on monthly routine immunization day, weekly morning Gram Sabha, and weekly Mahila Mandal meetings.

Training will be delivered in Hindi and Santhali (tribal) language, other tribal language such as Ho and Mundari can be incorporated as per need and demand from the study participants.

Evaluation of the feedback of participants towards the awareness booklet through a feedback form will be done after the training sessions. Feedback after training will cover the questions related to the training session, time, pace, and satisfaction of the participants. Whereas feedback for booklet will cover the content appropriateness, satisfaction, understanding the content, and effectiveness of local language. Table 1 below, represents the name of the eight healthcare schemes of India that will be included in the study.

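### The only association test named is chi-square and the KAP score is reduced to three bands; testing the score itself, or respecting the order of the bands, would recover up to about 20 points of power

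*Protocol article*

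**What the plan says.** All of this stands in the Sampling subsection of Methods/design in the protocol article, including the text after Figure 2.

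- **Test.** The analysis for objective 1 and for the objective 3 feedback form "will be descriptive data analysis and chi-square test to know the association between two variables". The later text repeats this: "Quantitative data analysis in terms of frequency, percentage, proportion and for categorical data chi square test will be done". No test on a numeric score (t-test, rank test, regression) and no ordered test (trend, ordinal model) is named.
- **Score.** "KAP score will be calculated and based on the median and interquartile range which will be finally interpret as low, moderate and high KAP score". The exact cut-points are not given.
- **Sample size.** It rests on the precision of one proportion, "keeping the level of confidence (z) at 95%, and marginal error(E)at 5%, population proportion 50% and population size 258454", and then: "Considering the drop out of 20%, with design effect of 1.5, the sample size becomes 385 (385 + 337) = 722 rounding up to 745". No power, effect size or SD is given for any association.
- **Allocation.** Twelve villages, with "tribal adolescent girls (n = 32/village") for girls and "n = 30 per village" for women.

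**The concern.** The survey yields a numeric score for each participant. Chi-square takes categories, so the score as a whole can enter it only as bands. Two losses follow. A participant just above a cut counts the same as one far above it. The Pearson test also treats low, moderate and high as unordered labels, so it spends 2 degrees of freedom where the question, whether one group scores higher than another, needs 1.

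At stake is the chance of detecting a real, moderate difference in KAP between socio-demographic groups. The opening of Methods/design says that survey data collection ended on 2 September 2024, so recruitment cannot buy this power back. A better use of the scores already collected can.

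**Working it through.** **1. The article's own figure.** 1.96² × 0.5 × 0.5 / 0.05² = 384.1, taken as 385. Then 385 × 1.5 = 577.5, and 577.5 / 0.8 = 721.9, so 722. This matches. The village allocation gives 12 × (32 + 30) = 744: 384 girls and 360 women.

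**2. Effective numbers,** using the article's design effect of 1.5:

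- all: 744 / 1.5 = 496
- all after 20% drop-out: 595 / 1.5 = 397
- women only: 360 / 1.5 = 240

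**3. Assumptions, because the article gives no figures.** The score is roughly normal. Two equal groups differ by d SD. Cuts lie at the pooled quartiles (25/50/25). The test is two-sided at 5%.

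**4. Formulas.**

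- Score (t-test): noncentrality n·d²/4, on 1 and n − 2 degrees of freedom.
- Three-band Pearson chi-square: noncentrality (n/2)·Σ(p − p̄)²/p̄ over the six cells, on 2 degrees of freedom (critical value 5.99).
- Trend test on the same bands (scores 0, 1, 2): noncentrality n·(difference in mean band score)²/(4 × band-score variance), on 1 degree of freedom.

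**5. Worked case, n = 496, d = 0.25.**

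- Score: 496 × 0.0625 / 4 = 7.75, power 79.3%.
- Bands: cell probabilities are 0.2895/0.50/0.2105 in one group and the reverse in the other. Each outer cell departs from 0.25 by 0.0395, so 248 × 4 × 0.0395² / 0.25 = 6.2. Power is 59.9%.
- Trend: the noncentrality is the same 6.2, but on 1 degree of freedom. Power is 70.2%.

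Banding therefore costs about 9 points here (79.3 to 70.2), and ignoring order costs about 10 more (70.2 to 59.9).

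**6. Range.**

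| Effective n | d (SD) | Score | Trend on bands | Chi-square on bands | Loss, score to chi-square (points) |
|---|---|---|---|---|---|
| 496 | 0.05 | 8.6% | 7.9% | 6.9% | 1.7 |
| 496 | 0.08 | 14.4% | 12.6% | 10.1% | 4.3 |
| 496 | 0.20 | 60.4% | 51.4% | 41.4% | 19.0 |
| 496 | 0.25 | 79.3% | 70.2% | 59.9% | 19.4 |
| 496 | 0.30 | 91.5% | 84.6% | 76.5% | 15.0 |
| 496 | 0.40 | 99.4% | 97.7% | 95.2% | 4.1 |
| 397 | 0.25 | 70.0% | 60.5% | 50.0% | 20.0 |
| 240 | 0.30 | 63.9% | 54.5% | 44.3% | 19.6 |
| 240 | 0.60 | 99.6% | 98.2% | 96.2% | 3.4 |

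**7. Sensitivity.**

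- Over six group splits, with and without the design effect, the largest loss is 19.8 to 20.2 points with quartile cuts and 20.6 to 20.7 with cuts at thirds.
- Factors with more levels lose slightly more at worst (744 participants, equal groups, evenly spaced means): 21.6 points for three levels, 22.7 for four, 24.4 for six.
- A simulation with groups of 384 and 360 gave 76.8% against 56.6% at d = 0.20.
- A simulation with a skewed discrete score, 496 independent observations and a Wilcoxon test gave 76% against 57%, so the gap does not hinge on normality.

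**The case against.** **The band-by-factor test is inferred.** The article never says that the bands will be cross-tabulated with socio-demographic factors. The banding sentence could be meant for description only, and single categorical items could go straight into chi-square. This stands as a limit: the point applies to associations with the KAP score. For those, the article offers no other test, so the reading is the natural one.

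**The survey is mainly descriptive.** Objective 1 is to assess KAP, and the sample size was set for the precision of a proportion. This stands and lowers the weight of the point. A reader might infer that a missed association would misdirect the booklet to the wrong groups. The article does not support that: it plans one booklet for girls and women, built on the survey and the interviews and piloted in all twelve villages. Nothing there depends on a subgroup p-value.

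**Twenty points is a maximum.** This stands. A reader might take it as the general loss, or suppose that the gain is negligible only for large effects in the full sample. Neither holds: the loss is also small at 0.05 to 0.08 SD, and at 0.60 SD among women alone.

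**Pooling is an assumption.** Table 1 lists three schemes for girls and six for women, with one shared. A single score over all 744 may not exist, so the women-only figures may be the more realistic guide.

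**Intervals may be planned elsewhere.** An article condenses a fuller protocol, so its silence on confidence intervals is not held against it.

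**Conclusion.** The point holds as an efficiency gain. The article fixes chi-square as its only association test and reduces the score to three bands; if the two are combined, as the text suggests, power is lost for no stated benefit. Under the assumptions in step 3 of the working, a two-group comparison loses at most about 20 points, at moderate effects, and little at either extreme. About half of the loss comes from ignoring order and can be recovered without giving up the bands. Describing participants as low, moderate or high is not wrong in itself, and the main descriptive estimates are unaffected. The change is worth making because it is cheap, not because the survey is invalid without it.

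**What to change.** In the analysis text of the Sampling subsection, state that:

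- associations with KAP use the numeric score, separately for girls and women if their questionnaires differ;
- the analysis is a linear model reporting the difference with a 95% confidence interval, allowing for village by a random village intercept or by cluster-robust standard errors with a small-sample correction, since there are only 12 villages;
- if the bands are tested, a trend test or an ordinal model is used;
- the low/moderate/high bands are kept for description, and Pearson chi-square for nominal items.

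This takes a few sentences and no new data or participants. The cost is a little more analysis work and care with the small number of villages. As the survey data are already collected, the change should be dated and made before the associations are examined, or reported as a later change if they already have been.
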